#### **Randomisation procedure (RYGB)**

If a patient has signed the Informed Consent form and is eligible for the trial the investigator will proceed as follows:

- Assignment of a Patient-ID: In the patient identification list (PIL, see investigator site file), fill in the patient personal data at the first free position of the list. The Patient-ID printed in the list at this position is assigned to the patient and will be used throughout the study as a pseudonym for the patient.
- Login at the randomisation-site, preferably via the MS Internet Explorer. The user will be asked for the Patient-ID, for check of eligibility criteria, presence of informed consent in writing and stratification items. Enter these items and then click the randomisation button. The system will return to you the intervention arm of the patient.

### **Study-Interventions (stRYGB and cIIRYGB):**

Two weeks' prior the bariatric surgery, patients undergo a low energy and protein-rich diet. The time interval between baseline/randomisation and bariatric surgery should not exceed 8 weeks. Details see chapters 5.1.

### **Discovery of a Violation of the Eligibility Criteria after the Fact**

In general, the violation of eligibility criteria is not a reason for premature withdrawal of the patient from the trial therapy or from the whole trial.

If after randomisation it is discovered that the patient was not eligible at the time of randomisation, this has to be reported to the KKS-Data Management as soon as possible. The KKS-Data Management informs the investigator immediately as to what is to be done with the patient. The patient's data will continue to be recorded.

According to the consent form, data or tissue will be stored as long as the patient agrees.

If the patient does not meet the inclusion criteria or has to be excluded from the study, the follow up will be performed according to the study protocol as long as the patient agrees (intent to treat). Otherwise, all patients will undergo the routine bariatric follow-up as long as they show up at our clinic.

## **6.4 Description of further Study Visits**

### **Visit 2 (postinterventional after 4 weeks ( $\pm$ 1 week))**

During Visit 2, the following procedures will be performed:

- Obtain comorbidities, concomitant medication and vital signs and perform physical examination (body weight, BMI, WHR, pulse, RR etc.)
- Routine fasting blood sample (fasting glucose, fasting insulin, fasting c-peptide, HbA1c, serum lipids, Adipokines, inflammatory markers, markers of kidney and liver function etc.)
- Assess Adverse Events since intervention

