| Indirect calorimetry                                                                                                                        | X                                      |                |                | X               | X                |                  |                  |                    |
| adverse events                                                                                                                              | X                                      | X              | X              | X               | X                |                  |                  |                    |

 The timing of the follow-up visits based on the date of the intervention for patients in the intervention groups and based on the date of the baseline examination for control patients.

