## 5 TRIAL INTERVENTION

### 5.1 Standard RYGB (stRYGB) group and Changed limb length RYGB (cllRYGB) group

Prior to surgery all candidates will be put on a low calorie (protein rich) diet for 14 days.

Roux-en-Y gastric bypass (stRYGB and cllRYGB) reduces the size of stomach to a small pouch – about the size of a walnut (pouch volume 10-20 cm^3), by stapling off a section of it. The surgeon then attaches this pouch directly to the small intestine, bypassing most of the stomach and the upper part of the small intestine.

All patients in the stRYGB group will undergo surgery with pouch size: 10 to 20 cm^3 and limb length:

- BMI  $\geq$  50 kg/m^2: alimentary limb: 170 cm, biliopancreatic limb: 80 cm).
- BMI  $\leq$  50 kg/m^2: alimentary limb: 150 cm, biliopancreatic limb: 50 cm).

All patients in the cllRYGB group will undergo bypass surgery with pouch size: 10 to 20 cm^3 and limb length:

- BMI  $\geq$  50 kg/m^2: alimentary limb: 80 cm, biliopancreatic limb: 170 cm).
- BMI  $\leq$  50 kg/m^2: alimentary limb: 50 cm, biliopancreatic limb: 150 cm).

RYGB (stRYGB and cllRYGB) will be done as a laparoscopic surgery. Laparoscopic surgery is performed using several small incisions, or *ports*: one to insert a surgical telescope connected to a video camera, and others to permit access of specialized operating instruments. The surgeon views his operation on a video screen.

[figure not shown]

Grafic 1: Standard RYGB (stRYGB)

Due to the reduced size of the newly created stomach pouch and reduced food intake, adequate nutrition demands that the patient follow the surgeon's instructions for food consumption, including the number of meals to be taken daily, adequate protein intake, and the use of vitamin and mineral supplements. Calcium supplements, iron supplements, protein supplements, multi-vitamins (sometimes pre-natal vitamins are best), and vitamin B12 (cyanocobalamin) supplements are all very important to the post-operative bypass patient.

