### **Visit 3 (postinterventional after 3 months ( $\pm$ 1 week))**

During Visit 3, the following procedures will be performed:

- Obtain comorbidities, concomitant medication and vital signs and perform physical examination (body weight, BMI, WHR, pulse, RR etc.)
- LiMAX test

- MRI examination by a trained radiologist
- Routine fasting blood sample (fasting glucose, fasting insulin, fasting c-peptide, HbA1c, serum lipids, Adipokines, inflammatory markers, markers of kidney and liver function etc.)
- Assess Adverse Events since last visit

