## 8 ADVERSE EVENTS (AE/SAE)

### 8.1 Adverse Events (AE)

#### 8.1.1 Definitions

The Declaration of Helsinki and the ICH-GCP Guideline E6 (point 4.11 and 5.17) set the protection of participants in clinical trials in the first place. Therefore, the safety and harmlessness of interventions and therapies without drugs have to be proved in clinical trials.

**Adverse Events (AE)** are all in patients occurring adverse medical events, unintended disease or injuries or undesirable clinical diagnoses (including abnormal laboratory results), regardless of whether these are related to the investigation or not.

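### The adverse-event look-back at Visits 1 and 2 starts at the intervention, so the visit lists do not prompt for events between randomisation and surgery, in conflict with section 8.1.2

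*Protocol*

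**What the plan says.** Section 6.3 lists the procedures of the enrolment and randomisation visit (Visit 1), and section 6.4 those of Visits 2 to 5. The adverse-event line at Visit 1 and at Visit 2 is the same: "Assess Adverse Events since intervention". At Visit 3 it becomes "Assess Adverse Events since last visit", and Visits 4 and 5 follow Visit 3.

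On the timing of surgery, section 6.3 says: "The time interval between baseline/randomisation and bariatric surgery should not exceed 8 weeks". Section 5.1 adds: "Prior to surgery all candidates will be put on a low calorie (protein rich) diet for 14 days". The footnote to the Schedule of Assessments and Procedures sets the visit clock "based on the date of the intervention for patients in the intervention groups and based on the date of the baseline examination for control patients". The schedule marks adverse events at Visits 1 to 5 and has no numbered visit between Visit 1 and Visit 2.

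The general safety text is wider. Section 8.1.2 has patients asked about adverse events at every visit, with no look-back period given, and also asks them to report events to the study management. Section 8.4 makes any new or worsened concomitant disease an adverse event, with no restriction to the time after surgery. Section 9.2.3 says that safety will be assessed by tabulating adverse and serious adverse events.

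**The concern.** The visit lists are the only places that tell the site which period to ask about. At Visit 1 the stated period does not yet exist for a surgical patient. At Visit 2 it begins at the operation. The stretch from randomisation to surgery falls between the two, and staff or a CRF prompt that follows the lists literally would not ask about it.

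This stretch is not idle time. It contains a diet that the protocol requires of every surgical candidate. Current insulin treatment is a stratification factor (9.1), so insulin-treated patients are expected among them. For the LiMAx subset it also contains test injections around the diet (15.1). It is when an event that delays or cancels surgery would occur, and a randomised patient who is never operated on has no period since surgery at all. Section 12.2 dispenses with a data monitoring safety board, so the safety record rests largely on what the site collects at visits.

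At stake are the completeness of the adverse-event tables for the surgical arms and the comparability of those tables with the control group.

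**Working it through.** The protocol states no figure on this point, so the check sets the sections side by side and adds calendar arithmetic.

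**1. What intervention means here.** The term is not defined. Section 6.4 heads Visit 2 as "postinterventional after 4 weeks", and the schedule footnote reads: "The timing of the follow-up visits based on the date of the intervention for patients in the intervention groups". Section 6.3 treats baseline/randomisation and surgery as separate dates. Together these point to the operation as the start of the look-back.

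**2. Look-back by visit in the surgical arms, on that reading.**

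| Visit | Stated look-back | Period covered |
|---|---|---|
| 1 (baseline, randomisation) | from the intervention | none, as surgery has not happened |
| 2 (4 weeks ± 1 week after surgery) | from the intervention | surgery to Visit 2 |
| 3, 4, 5 | from the previous visit | continuous from Visit 2 |

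The uncovered stretch is randomisation to surgery. Had Visit 2 used the wording of Visits 3 to 5, the gap would be 0 weeks.

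**3. Size of the gap.** Inputs: up to 8 weeks from randomisation to surgery (6.3), 14 days of diet (5.1), Visit 2 at 4 ± 1 weeks after surgery (6.4).
- Weeks after surgery at Visit 2: 4 − 1 = 3 to 4 + 1 = 5.
- Weeks after randomisation at Visit 2, with an 8-week wait: 8 + 3 = 11 to 8 + 5 = 13.
- Share of that time inside the Visit 2 look-back: 3/11 = 27% to 5/13 = 38%.
- Weeks outside it: 8, of which 2 are the diet.
- If the diet were counted as part of the intervention: 8 − 2 = 6 weeks outside.

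**4. Controls.** They have no operation, and their visit clock starts at the baseline examination. Reading the Visit 2 look-back for them as running from baseline, their first weeks in the trial are covered and there is no matching gap.

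**5. Against section 8.**
- 8.1.2 requires a question at each visit with no time limit, whereas 6.3 and 6.4 limit the period at Visits 1 and 2. These conflict.
- 8.4 brings new or worsened disease into adverse events whenever it occurs, and Visit 2 also obtains comorbidities and concomitant medication. This gives a second route by which a pre-operative event can reach the record.
- No section states when adverse-event collection begins.

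**The case against.** The strongest reply is that section 8.1.2 already closes the gap. It requires active questioning at every visit, not just spontaneous reports, and sets no window. Section 8.4 captures new or worsened disease, serious events carry no time limit in 8.2, and section 6.5 has reasons for premature termination reported and all patients followed up completely. This stands to a large extent. A reader might infer that the pre-operative period is never asked about, and the documents do not support that. What 8.1.2 does not do is say which period the question covers. The visit lists do say, and they say something narrower, so the two need reconciling.

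A reader might also see a contradiction with section 8.1.1, which counts events "regardless of whether these are related to the investigation or not". That clause concerns causality, whereas the visit wording concerns time. The two are compatible.

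It can further be said that intervention may include the diet, because sections 5.1 and 6.3 describe the diet under intervention headings. The ambiguity is real, but the Visit 2 heading and the schedule footnote favour surgery. Even the wider reading leaves up to about 6 weeks uncovered.

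Finally, the effect on the planned analyses is limited. The synopsis, 9.2.3 and 9.3.2 place weight on procedure-related events and complications, most of which arise after surgery. This is right, and it confines the issue to the general tabulation of adverse and serious adverse events in 9.2.3.

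**Conclusion.** The point holds as a conflict between sections 6.3/6.4 and 8.1.2. On the natural reading, the stated look-backs omit up to about 8 weeks per surgical patient, including the 14-day diet, and the Visit 1 instruction has no content. The 8 weeks is a recommended limit, so an individual gap may be shorter or longer.

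The consequence is possible incompleteness of the adverse-event and serious-adverse-event tabulation in the surgical arms, and a window that differs from that of the non-randomised controls. The look-back rule is identical in the two randomised surgical arms, so this wording does not bias the comparison between them.

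The number of missed events cannot be estimated. It is tempting to multiply the 68 + 68 = 136 planned surgical patients by 8 weeks and call the product lost observation time. That would assume that every patient waits the full interval and that 8.1.2 prompts for nothing. The protocol gives neither a distribution of waiting times nor an adverse-event rate.

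The conclusion rests on two assumptions: that intervention means surgery, and that sites follow the visit lists as written. The CRF prompts are not in the document and might already ask more widely.

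**What to change.** Reconcile 6.3 and 6.4 with 8.1.2:
- State once, in 8.1.2, that adverse-event collection starts at Visit 1 after consent.
- In the Visit 1 list, delete the reference to the intervention.
- In the Visit 2 list, have adverse events assessed since Visit 1 (baseline).
- Apply the same collection from baseline to randomised patients who are not operated on.

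The adverse-event CRF page already records start and end of each event (8.1.2). With the date of surgery, events can be split into before and after the operation.

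The cost is a few lines of text and a check of the CRF prompt, with no extra visit. The downside is slightly higher adverse-event counts in the surgical arms, and the split at surgery makes that increase visible for what it is.

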### **Visit 3 (postinterventional after 3 months ( $\pm$ 1 week))**

During Visit 3, the following procedures will be performed:

- Obtain comorbidities, concomitant medication and vital signs and perform physical examination (body weight, BMI, WHR, pulse, RR etc.)
- LiMAX test

- MRI examination by a trained radiologist
- Routine fasting blood sample (fasting glucose, fasting insulin, fasting c-peptide, HbA1c, serum lipids, Adipokines, inflammatory markers, markers of kidney and liver function etc.)
- Assess Adverse Events since last visit

#### **Visit 4** (postinterventional after 6 months ( $\pm$ 2 weeks))

During Visit 4, the following procedures will be performed:

- Obtain comorbidities, concomitant medication and vital signs and perform physical examination (body weight, BMI, WHR, pulse, RR etc.)
- Routine fasting blood sample (fasting glucose, fasting insulin, fasting c-peptide, HbA1c, serum lipids, Adipokines, inflammatory markers, markers of kidney and liver function etc.)
- BIA-measurement (performed by a trained nurse)
- Indirect calorimetry
- Ultrasound scan (liver, fibroscan, IMT)
- MRI examination by a trained radiologist
- LiMAx test
- Assess Adverse Events since last visit

#### **Visit 5** (postinterventional after 12 months ( $\pm$ 1 month))

During the Visit 5, the following procedures will be performed in all patients:

- Obtain comorbidities, concomitant medication and vital signs and perform physical examination (body weight, BMI, WHR, pulse, RR etc.)
- Routine fasting blood sample (fasting glucose, fasting insulin, fasting c-peptide, HbA1c, serum lipids, Adipokines, inflammatory markers, markers of kidney and liver function etc.)
- Indirect calorimetry
- Assess Adverse Events since last visit
- Ultrasound scan (liver, fibroscan, IMT)
- MRI examination by a trained radiologist
- BIA-measurement (performed by a trained nurse)
- Diet protocol
- Assess detailed quality of life (SF36) and physical activity (IPAQ)

## **6.5 Premature Termination of the Therapy or Follow-up**

The date (as exactly known as possible) and if possible the circumstances and reasons for every premature termination of the therapy or follow-up will be reported to the KKS-Data Management.

Non-compliance is a common issue in trials. We define non-compliance as significant deviation from the study protocol, specifically missing more than two study visits. All patients, whether compliant or not, shall be followed-up completely.

### 6.5.1 Premature Termination of the Therapy for Individual Patients

The study participation will be interrupted or terminated if

- the physician decides to
- the patient cannot be reached for more than two missed visits
- if informed consent is withdrawn
- the patient becomes pregnant.

Patients excluded from the study will be reported to the KKS-Data Management. The information will include the date, when known, circumstances and reasons, whether the patient is available for further follow up investigations and whether he/she is available for the routine bariatric follow up or not.

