## 9.5 Statistical Methods

### 9.5.1 Analysis Population

The main analyses will be performed for the per-protocol (PP) population in all three groups, including the observational arm. Only patients who received the planned treatment and provide data for the primary endpoint will be counted amongst the PP population.

Secondary analyses will be performed for the intention to treat (ITT) population in all three groups, including the observational arm. Missing HbA1c data will be accounted for using multiple imputation. If a patient does not provided data regarding diabetes remission, then this patient will be treated as not having had remission in the analysis.

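### Sections 6.5 and 6.5.1 conflict on whether a patient whose study participation is ended early is still followed to the 12-month HbA1c

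*Protocol*

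**What the plan says.** Section 6.5 defines non-compliance as a significant deviation from the protocol, "specifically missing more than two study visits", and then sets the follow-up rule: "All patients, whether compliant or not, shall be followed-up completely".

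Section 6.5.1 is headed as dealing with termination of therapy, but its list opens with "The study participation will be interrupted or terminated if". Two of its four reasons matter here. One is simply that the physician decides to, with no limit or criterion. The other is that "the patient cannot be reached for more than two missed visits". The section then speaks of these patients as excluded and asks that a report state, among other things, "whether the patient is available for further follow up investigations".

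Section 6.5.2, on ending follow-up, says only that such events are documented. It gives no criteria.

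Section 6.3, under the heading on eligibility violations discovered after the fact, says that a patient who has to be excluded continues in protocol follow-up while he or she agrees, and labels this intent to treat.

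Section 9.5.1 makes the per-protocol population the basis of the main analyses: "Only patients who received the planned treatment and provide data for the primary endpoint will be counted amongst the PP population". The ITT analysis is secondary. It uses multiple imputation for missing HbA1c and counts missing remission data as no remission.

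**The concern.** Section 6.5 tells the site to keep following these patients. Section 6.5.1 lets it end their participation and regard them as excluded. Because 6.5.1 mixes therapy (in its heading) with participation (in its text), and 6.5.2 is silent, a site has no clear instruction on whether to seek the Visit 5 blood sample.

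In the surgical arms the intervention is a single operation. Once it has been done, ending participation withdraws no surgery and mainly affects whether data are still collected.

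At stake is the completeness of the primary endpoint. Each patient ended early without a 12-month HbA1c drops out of the main analysis. If such endings depend on arm or on how the patient is doing, the loss is not random. The physician item is the more exposed of the two: the trial is open, and Section 3.1 promises visit staff unaware of the surgical procedure only where logistics allow.

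**Working it through.** **1. When the missed-visit item can act.** More than two missed visits means at least 3. Between the intervention and Visit 5, Section 6.4 schedules Visit 2 ("postinterventional after 4 weeks"), Visit 3 ("postinterventional after 3 months") and Visit 4 (6 months), which is exactly 3 visits. Before the primary endpoint the threshold is therefore met only if all three are missed. The earliest point is Visit 4, which is 12 − 6 = 6 months before Visit 5, although Visit 5 is then the next scheduled visit. The schedule also lists Visits 6 to 8, so the item can apply after the primary endpoint has been collected.

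**2. The two sections side by side, before Visit 5.**

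| Situation | Section 6.5 | Section 6.5.1 | Conflict |
|---|---|---|---|
| One or two visits missed | follow up | missed-visit item not met | none |
| Visits 2 to 4 missed, patient reachable | non-compliant; follow up completely | missed-visit item not met | none on this item |
| Visits 2 to 4 missed, patient unreachable | non-compliant; follow up completely | participation interrupted or terminated | yes, but overlaps with loss to follow-up |
| Physician decides, any attendance | follow up completely | participation interrupted or terminated | yes, without limit |

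**3. Whether other text settles it.** Recording availability for further follow-up does not instruct anyone to obtain the HbA1c. Section 6.3 does continue follow-up after exclusion, but it stands under eligibility violations and 6.5.1 does not refer to it. It shows the intent without resolving the conflict.

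**4. What follows in the analysis.** Without a 12-month HbA1c the patient fails the per-protocol definition. In the ITT analysis the value is imputed and remission is set to no. A patient who missed Visits 2, 3 and 4 has no post-baseline HbA1c to inform the imputation. A patient ended by physician decision may have some.

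**5. Whether the size can be computed.** The planning figures in Section 9.4 are not disputed and reproduce:
- Power: the difference is 2.9 − 1.4 = 1.5 and the standard error is √(1.5²/17 + 1.7²/119) = 0.396. A two-sided 5% Welch t-test then has 95.2% power, against the stated 95% (two-sided testing is my assumption).
- Drop-out: 17 + 119 = 136, and 136/(1 − 0.15) = 160 = 24 + 68 + 68.

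The 15% allowance is not split by cause. The number of endpoints lost to the rule would be the number enrolled × the share meeting a trigger × the share of those whose value could otherwise have been obtained. The resulting shift in an arm contrast would be roughly the difference in lost share × the HbA1c gap between lost and retained patients. The protocol gives none of these shares or gaps, so neither quantity can be computed.

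**The case against.** The strongest reply is that the contradiction is narrower than it looks. Missed visits alone do not trigger 6.5.1, because the patient must also be unreachable. A reachable non-compliant patient stays under 6.5, and an unreachable one cannot be followed whatever the protocol says. Participation may be interrupted rather than ended, availability for further follow-up is recorded, and Section 6.3 shows that the sponsor means to follow excluded patients. Unreachable patients are ordinary loss to follow-up, which the 15% allowance already covers.

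Most of this stands for the missed-visit item, and it limits what may be claimed. A reader might infer that 6.5.1 removes patients merely for missing visits, or that it is timed to strike just before the endpoint. The text supports neither: the first drops the unreachability condition, and the second needs all of Visits 2 to 4 missed and still leaves about six months.

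Two things survive. A patient unreachable at month 6 may be reachable at month 12, and 6.5 calls for the attempt while 6.5.1 lets it lapse. And the reply does not touch the physician decision, which has no reachability condition and no limit. Keeping surgical patients unaware of their procedure does not help there, because the decision is the physician's.

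**Conclusion.** The conflict between 6.5 and 6.5.1 is real and, with 6.5.2 silent, leaves the handling of the primary endpoint unclear for patients ended early. The missed-visit item adds little beyond ordinary loss to follow-up. The open-ended physician decision is the larger gap. The result is avoidable, and possibly arm-related, missing 12-month HbA1c values in a trial whose main analysis excludes patients without one.

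The size is unknown. A reader might put figures on it, for example 3 to 5% of the 136 surgical patients (4 to 7 endpoints), or a 5-point difference in loss between arms times a gap of 1.0 to 1.5 HbA1c points (a shift of 0.05 to 0.08). None of these inputs is in the protocol. They also fit together poorly: with equal arms and a 3% average, a 5-point difference means about 0.5% against 5.5%. Even that shift would be small beside the planned difference of 1.5. Nor does the protocol say that patients meeting the rule have worse HbA1c. The point therefore rests on the contradiction and the avoidable loss of endpoint data. It does not rest on a demonstrated bias or a failure of power.

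**What to change.** Reconcile Sections 6.5, 6.5.1 and 6.5.2 with the follow-up statement in Section 6.3:

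- In 6.5.1, separate ending therapy or scheduled visits from ending data collection. State that a physician decision, missed visits or temporary unreachability does not end data collection.
- In 6.5.2, state that data collection ends when consent to it is withdrawn.
- State that contact is attempted again at month 12 to obtain the Visit 5 HbA1c from every enrolled patient, in all three groups, unless that consent has been withdrawn.
- Apply the Section 6.3 principle of continued follow-up explicitly to patients ended under 6.5.1.

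This is protocol wording and changes no clinical rule; how any listed reason is managed clinically is not at issue. The downside is a small extra effort to contact these patients. Section 1.1 plans lifelong follow-up at the centre and Section 1.3 ties study blood samples to routine ones, so the value should often be obtainable without much added burden.
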